#### Secondary outcomes

Cognitive performance as measured by immediate and delayed recall of a short story, tests of prospective memory, timed letter search/cancellation task, verbal fluency, digit span forwards and backwards, symbol digit modalities test, simple and choice reaction time, and spatial memory.

Psychological health.

Compliance determined by counting the number of capsules remaining every 3 months, and by measuring the change in n-3 LCP concentration in buccal epithelial cells over 24 months.

Blood pressure.

Change in Body Mass Index (a measure of body size).

Number of hospital admissions for cardiovascular events over 24 months.

Death.

### Sample size

The sample size required for this trial is based on a 0.3SD difference between trial arms in long-delay free recall of List A of the California Verbal Learning Test over the 24 months of intervention. To detect a 0.3SD difference between trial arms, with 90% power and 1% significance, 332 individuals are required per treatment group. Allowing for 20% drop-out over 24 months of intervention, the total sample size required for the study is 798 individuals. A difference of 0.3SD is clinically relevant and would be equivalent to individuals in the intervention arm being able to remember one more word out of the 16 in the California Verbal Learning Test than those in the placebo arm [18].

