Individuals giving informed consent will be enrolled in the trial. The research nurse will telephone the central randomisation service to register the participant, giving identifying details and the participant's age. Randomisation will allow secure blind allocation of eligible people to one or other arm of the study. Following random allocation a study number will be given for each study participant. This will also be used to identify the supply of capsules to be prescribed for each participant. The study number will be entered on the participant's entry form. Pre-labelled identical-looking packs of capsules (see *Dietary Intervention *below) will be stored securely in the general practice. Minimisation criteria will be used to ensure a balance of key prognostic factors using the following two criteria: age group (70–74 and 75–79 years) and general practice.

Participants will then be assessed by completing questionnaires and undertaking a series of tests (see *Baseline Data Collection *below). The full set of baseline tests will take approximately 60 minutes to complete. Any couples recruited to the study will undertake their assessments separately. Participants will be provided with the contact details of the study nurses and trial manager. Information will also be available from the trial web-site [17] for those participants who wish to use this method of obtaining information. Participants will be thanked for their time and co-operation.

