### Sample size

The calculation for the sample size required to demonstrate a significant difference between the placebo and intervention arms of the trial is based on the decline in rod sensitivity with age [14]. In line with previous studies on the effect of DHA during infant development, we anticipate that an increase in dietary intake of DHA will significantly improve rod sensitivity; increases of the order of +2SD in rod sensitivity have been demonstrated in studies of DHA supplementation in preterm infants [23,24]. Considering the complexity of the study and the limited significance of small changes in retinal sensitivity we have defined a biologically significant effect as an increase of 1SD. To detect this effect with 90% power and 5% significance, the sample size required is 22 per group. Allowing for 25% drop-out during the trial, the total sample size required for this sub-study is 56 individuals.

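### Both drop-out allowances multiply by (1 + d) instead of dividing by (1 − d), so 798 and 56 leave about 319 and 21 completers per arm, not the 332 and 22 required (minor)

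*Protocol article*

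**What the plan says.** Protocol article, Cognitive function study, Sample size: the calculation is "based on a 0.3SD difference between trial arms in long-delay free recall of List A of the California Verbal Learning Test" and concludes that, "with 90% power and 1% significance, 332 individuals are required per treatment group". The next sentence adds the allowance for loss: "Allowing for 20% drop-out over 24 months of intervention, the total sample size required for the study is 798 individuals".

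Protocol article, Retinal function study, Sample size: "we have defined a biologically significant effect as an increase of 1SD", and "To detect this effect with 90% power and 5% significance, the sample size required is 22 per group". The allowance follows: "Allowing for 25% drop-out during the trial, the total sample size required for this sub-study is 56 individuals".

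Neither section gives the inflation formula, the sidedness of the test or an allocation ratio. The (ii) Patients section describes two arms: "Randomisation will allow secure blind allocation of eligible people to one or other arm of the study". One sample size is quoted per group, so I take allocation as 1:1.

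**The concern.** A drop-out rate d is a share of those enrolled, so N enrolled leaves N × (1 − d). To finish with n completers, a trial must enrol n / (1 − d). Enrolling n × (1 + d) always falls short, because (1 + d)(1 − d) = 1 − d², which is less than 1. At d = 0.20 this delivers 96% of the completers needed, before rounding; at d = 0.25 it delivers 93.75%.

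Each section states three figures: completers needed per arm, expected loss and total to enrol. In both sections the three cannot all be right. At stake is whether the quoted 90% power holds under the plan's own attrition assumption, for the two hypotheses that the Design section calls primary.

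**Working it through.** **Inputs**, from the two Sample size sections:
- Cognitive: difference 0.3 SD, significance 1%, power 90%, 332 per arm, d = 0.20, total 798.
- Retinal: difference 1 SD, significance 5%, power 90%, 22 per arm, d = 0.25, total 56.
- Assumed: two-sided tests and 1:1 allocation. The drop-out arithmetic does not depend on sidedness.

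**Step 1. Per-arm figures.** Normal approximation, n = 2(z₁₋α/₂ + z₁₋β)² / δ².
- Cognitive: 2(2.576 + 1.282)² / 0.3² = 330.7, so 331. The t-test gives 333. The protocol's 332 lies between them.
- Retinal: 2(1.960 + 1.282)² / 1² = 21.01, so 22, as stated. The t-test gives 23.
- One-sided tests would give 290 and 18, which do not match.

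The figures 332 and 22 are therefore sound, and two-sided testing is the reading that fits them.

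**Step 2. Reproducing the stated totals** with n × (1 + d), rounded up per arm.
- Cognitive: 332 × 1.20 = 398.4 → 399; 399 × 2 = 798. Exact match.
- Retinal: 22 × 1.25 = 27.5 → 28; 28 × 2 = 56. Exact match.

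**Step 3. Totals from n / (1 − d).**
- Cognitive: 332 / 0.80 = 415; 415 × 2 = 830, which is 32 more than 798.
- Retinal: 22 / 0.75 = 29.33 → 30; 30 × 2 = 60, which is 4 more than 56. If only the total is rounded up, 44 / 0.75 = 58.67 → 59, which is 3 more.

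**Step 4. Completers left by the stated totals.**
- Cognitive: 798 × 0.80 = 638.4, about 319 per arm against 332.
- Retinal: 56 × 0.75 = 42, or 21 per arm against 22.

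**Step 5. Power at those numbers** (two-sided).

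| Study | Completers per arm | t-test | Normal approximation |
|---|---|---|---|
| Cognitive, 0.3 SD, 1% | 332 | 89.97% | 90.1% |
| Cognitive, 0.3 SD, 1% | 319 | 88.6% | 88.7% |
| Retinal, 1 SD, 5% | 22 | 89.97% | 91.3% |
| Retinal, 1 SD, 5% | 21 | 88.5% | 89.98% |

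**Step 6. Loss at which the stated totals still leave the required completers.**
- Cognitive: 1 − 664/798 = 16.8%.
- Retinal: 1 − 44/56 = 21.4%.

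**The case against.** The arithmetic itself is hard to dispute. The case on the other side is that it matters little, and most of that case stands.

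- **The effect on cognitive power is small.** It falls by about 1.4 points. The effect detectable with 90% power moves from 0.300 SD to about 0.300 × √(332/319) = 0.306 SD. The significance level, the analysis and the meaning of the result do not change. This stands.
- **The retinal power loss depends on the method.** The normal approximation needs 21.01 per arm, so 21 completers give 89.98%, which is 90% at the precision the protocol uses. Only the t-test shows a visible loss, and by that test 22 itself falls just short of 90%. This stands.
- **The loss of power is conditional.** It arises only if drop-out exceeds 16.8% or 21.4%. The 20% and 25% are planning allowances, and the protocol gives no source for either. This stands, though 20% and 25% are the rates the plan chose to allow for.
- **Covariate adjustment may recover the loss.** Both data analysis sections plan adjustment, for which the sample sizes take no credit. If the covariates had a multiple correlation R with the outcome, the missing completers would be offset when 1 − R² = 319/332 (R about 0.20) or 21/22 (R about 0.21). The documents do not give R, so this is only an assumption. It does not correct the stated totals.

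A reader might infer that both studies have less power than they report, or that the trial is underpowered. The documents do not support either inference. A power shortfall that holds under both standard methods is shown only for the cognitive study, only if the assumed loss occurs, and it is under 2 points.

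None of this reconciles the figures. For 798 to be right, the 20% would have to be a share of completers, and the protocol does not define it that way.

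**Conclusion.** Wrong as written, of minor severity. Both totals are matched exactly by the wrong inflation rule and neither by the right one, which points to one repeated slip and not to rounding. Under the plan's own loss rates the totals are short by about 13 completers per arm in the cognitive study (332 − 319) and by one per arm in the retinal sub-study (22 − 21). That part needs no assumption beyond equal arms.

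The effect on power is less firm. With two-sided tests and the full assumed loss, the cognitive study has about 88.6% power (t-test), not 90%. For the retinal sub-study the result is 88.5% or 89.98% according to method, so a loss of power there should not be asserted without naming the method.

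**What to change.** Keep 798 and 56 and restate one sentence in each Sample size section, in either of two ways:

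- With 20% loss about 319 per arm remain, giving about 88.6% power; with 25% loss 21 per arm remain, giving about 88.5% power (both by two-sided t-test).
- The totals retain 332 and 22 per arm for losses of up to 16.8% and 21.4%.

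This costs two sentences, no additional participants and no change to the analysis. The first option does require accepting stated power slightly below 90%.

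If the sponsor prefers to keep 90% power at the stated losses, the targets become 830 and 60 (59 if only the total is rounded up). That means enrolling 32 and 3 to 4 more people, so it is the dearer option. For the cognitive study it fits the plan's own projection: the Recruitment section expects 20% of about 4500 to agree, which is 900 and exceeds 830. The protocol gives no uptake rate for the retinal sub-study, so the same check cannot be made there.

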### Recruitment

In order to attain this sample size it is expected that a sample of approximately 4500 individuals, pre-screened for diabetes and dementia, will initially be drawn from the registers of 20 participating general practices (around 225 patients aged 70–79 years per practice). A conservative estimate of the proportion of eligible individuals who will agree to participate in the trial is 20%. It is estimated that it will take 6 months to enrol the full sample for this trial.

### Baseline (pre-intervention) cognitive function data collection

#### At trial entry to enable randomisation

Initials

Date of birth

Gender

General practice number

MMSE score

Consent

### Baseline data collection

1. Psychological health: the 30–item General Health Questionnaire (GHQ-30) will be used to assess the affective state of participants [19]. The GHQ-30 is quick and easy to administer, and an assessment of mood is important as it may be associated with cognitive performance.

2. Educational achievement: the widely used Burnham Scale of educational achievement will be used [20]. This is an important covariate as educational level has been shown to be strongly related to cognitive performance.

3. Blood pressure: this is necessary as hypertension is an important consequence of the metabolic syndrome, and individuals with high blood pressure may have a raised susceptibility to vascular and neural damage. Baseline blood pressure will therefore be used as a covariate in analysis. Blood pressure will be measured using the automated DYNAMAP device. Two measurements each of systolic and diastolic pressure will be taken in the sitting position (the mean of the two measurements will be used in analysis); participants will have rested for 5 minutes before their blood pressure is measured and there will be a minimum of 5 minutes between the two measurements. Normal general practice procedures will be followed for the management and treatment of high blood pressure.

4. Cardiovascular health: any history of hospital admission for myocardial infarction (MI) or stroke over the preceding 5 years will be abstracted from patient notes.

5. National Health Service number: So that the study organisers do not lose contact with patients should they move address and also to follow up on health status, participants are being asked to give their agreement for their names and NHS numbers to be sent to the NHS Central Register.

6. Basic anthropometric measures: height and weight will be measured using standardised procedures in order to enable the calculation of the Body Mass Index: a basic marker of body size.

7. Swab of cheek cells: nurses will collect a sample of buccal mucosal epithelial cells from each participant. This is a relatively non-invasive procedure in which a sterile wooden spatula is scraped briskly along the inside of the cheek (about 10 strokes on each cheek). The cheek cells will be sent to laboratories, in sterile containers, to be analysed for their n-3 LCP concentration.

8. Fish consumption: two simple questions regarding habitual fish consumption will be asked. Firstly, a question regarding the frequency of fish consumption, and second, participants will be asked to list the three species of fish they consume most frequently.

9. Cognitive ability: the participants will be asked to complete a validated series of cognitive tests. It is currently not known which, if any, cognitive domain will be most affected by n-3 LCP supplementation and therefore a series of tests have been selected which cover the major domains (memory, attention, psychomotor speed and executive function):

a. Brief assessment of subjective symptoms of cognitive impairment (memory, language/word-finding, concentration).

b. Immediate and delayed recall of a short story (from the Wechsler Memory Scale).

c. Immediate and delayed recall of a 16-item word list (California Verbal Learning Test).

d. Three tests of prospective memory i.e. remembering to carry out instructions without being reminded.

e. Timed letter search/cancellation task (attention/psychomotor speed/executive function).

f. Verbal fluency – naming animals (word-finding/executive function).

g. Digit span forwards and backwards (working memory/executive function) from the Wechsler Adult Intelligence Scale.

h. Symbol digit modalities test (attention/psychomotor speed/executive function).

i. Simple (psychomotor speed) and choice (decision speed) reaction time.

j. Spatial memory (memory/visual spatial function).

### Dietary intervention

Following the completion of the series of tests detailed above, those participants not enrolled in the retinal function study will be introduced to the dietary intervention. The dietary intervention will be a daily dietary supplement in the form of capsules which will be identical in size, shape, colour and smell for both the intervention and placebo arms of the trial. Given the lack of trial evidence to support the use of any particular level of dietary supplementation, the dose selected in the OPAL study was based on the following considerations: the UK Food Standards Agency currently recommends that men and post-reproductive age women consume one to four, 140 g portions of oily fish a week [21]; typical dietary recommendations, such as those of the World Health Organisation fall in the range 0.3–0.5 g n-3 LCPs daily [22]; the dose of n-3 LCPs generally recognised as safe (GRAS) is 3 g per day.

Taking these considerations into account, a pragmatic decision was made on the dose for the OPAL study. The intervention arm will be asked to consume two 650 mg soft-gel capsules daily containing a total of 500 mg DHA and 200 mg EPA. This is equivalent to approximately 4.9 g of n-3 LCPs a week (0.7 g/day), a level that can be achieved via the consumption of approximately 300 g (slightly more than 2 portions) of fatty-fish a week. This level of supplementation falls well below the upper GRAS level and should thus be safe. The placebo arm will be asked to consume two identical 650 mg capsules containing olive oil daily, this oil is rich in n-9 fatty acids and will thus have a minimal effect on the 18:2 n-6/18:3 n-3 ratio. Changes in the n-6/n-3 ratio may affect prostanoid balance which affects vascular and inflammatory responses. The higher DHA to EPA ratio in the supplement is justified by the rationale of the study, which prioritises the neuroprotective effect of DHA over the vascular and anti-thrombotic effect of EPA.

The research nurses will explain the importance of consuming the capsules every day, suggesting that it should become part of their daily routine, for example by always consuming the capsules at breakfast-time. Participants will be given a 3-month supply of capsules at the baseline clinic visit, and asked to attend the clinic every 3-months throughout the 24-month course of the trial i.e. at 3, 6, 9, 12, 15, 18 and 21 months. Participants will be sent reminders to collect repeat supplies of capsules.

The participants enrolled in the retinal function study will be introduced to the dietary intervention after their baseline retinal function test (see below). These participants will be invited back to the general practice after retinal function testing to be given their dietary supplements.

### Data collection at 3, 6, 9, 12, 15, 18, and 21 months

Participants will have appointments to meet the research nurse every 3 months throughout the study (8 repeat visits in total including 24 month assessment). During these appointments, participants will be reminded of the importance of the study and of the need to comply with the study protocol. The research nurses will also record any information the participants volunteer regarding any discomfort caused by the capsules. The recognised side-effects of n-3 LCP capsules include belching, flatulence, abdominal discomfort and loose stools. These discomforts are generally mild and decrease over time, and the research nurses will provide reassurance to any concerned participants.

Participants will be asked to bring their dietary capsule containers with them to the meeting so that any remaining capsules can be counted as a measure of compliance. Buccal cell swabs will also be taken during these repeat appointments from a random 20% sample every 6 months (i.e. at 6, 12 and 18 months) as a further measure of compliance. Participant records from the general practice will be consulted every 3 months in order to record any hospital admissions for MI or stroke over the intervening 3 month period.

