### Assessment at 24 months

A final evaluation of the cognitive function of all trial participants will be carried out after 24 months of intervention. Participants will be invited to attend their general practice and will be assessed for:

1. Psychological health: as at baseline.

2. Blood pressure: as at baseline.

3. Cardiovascular health: record of hospital admissions for MI or stroke between the 21 and 24 month appointments.

4. Basic anthropometric measures: as at baseline.

5. Buccal cell DHA concentration: as at baseline. Collected as a marker of the impact of the intervention on buccal cell DHA concentration, and compliance in the intervention arm of the trial.

6. Cognitive function: as at baseline.

Participants will be offered the use of a taxi, or their travel costs on public transport or mileage in private cars to attend the appointment up to a maximum of £10.

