### Data Monitoring Committee

An independent Data Monitoring Committee (DMC) will be established. The membership will comprise [name] (Chair), [name] (senior statistician) and [name] (clinician). The role of the DMC will be firstly to check on safety by random allocation. Although this intervention is not expected to lead to adverse consequences, it is important to guard against this eventuality. If necessary, this could lead to stopping the trial before knowing the primary outcome. Secondly the DMC will also look at on-going compliance data by random allocation to check that a difference in exposure is occurring. If a problem were to be detected, this could lead to a recommendation to amend aspects of the protocol. Thirdly, the DMC will consider data at trial entry by random allocation in order to be able to interpret the compliance and side effects data. The committee will meet at the start of the trial to agree terms of reference and then at the end of the recruitment period and every 6 months or as they determine.

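### Recording only volunteered, capsule-attributed discomfort weakens, but does not prevent, the monitoring committee's comparison of side effects and other non-fatal events by arm

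*Protocol article*

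**What the plan says.** The section on data collection at 3 to 21 months gives the nurses this rule: "The research nurses will also record any information the participants volunteer regarding any discomfort caused by the capsules". The next sentence lists what is expected: "The recognised side-effects of n-3 LCP capsules include belching, flatulence, abdominal discomfort and loose stools". The article calls these effects generally mild and has the nurses reassure anyone concerned. It does not say that they ask about them.

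The section on the 24-month assessment lists six items: psychological health, blood pressure, cardiovascular health, anthropometry, buccal cell DHA and cognitive function. None concerns side effects.

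The Data Monitoring Committee section states: "The role of the DMC will be firstly to check on safety by random allocation". It adds that harm is not expected but should be guarded against, and that "If necessary, this could lead to stopping the trial before knowing the primary outcome". The committee also sees entry data by arm "in order to be able to interpret the compliance and side effects data".

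Some safety information does not depend on what a participant says. Between 3 and 21 months, "Participant records from the general practice will be consulted every 3 months in order to record any hospital admissions for MI or stroke"; the 24-month list adds a "record of hospital admissions for MI or stroke between the 21 and 24 month appointments". The secondary outcomes include "Number of hospital admissions for cardiovascular events over 24 months" and death.

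**The concern.** The recording rule applies three filters. The participant must raise the matter unprompted, it must be a discomfort, and it must be put down to the capsules. A person aged 70–79 who has a new complaint and does not connect it with a supplement passes none of them reliably. Unexpected harm, which the committee section says it wants to guard against, is the kind a participant is least likely to attribute to a capsule.

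The committee's side-effect table could then show similar counts in the two arms partly because few events were captured. A reader of the final report could take that as evidence of good tolerability when it partly reflects how the events were collected.

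**Working it through.** **Sources of safety data set side by side**

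| Type of event | Route stated in the article | Depends on participant volunteering? |
|---|---|---|
| MI or stroke admission | Practice records every 3 months, and for months 21 to 24 | No |
| Death | Listed as a secondary outcome; how it is ascertained is not stated | Not stated |
| Eye changes, retinal sub-study only | Ophthalmic examination at baseline and 24 months, with fundus photography | No |
| The four recognised effects | Volunteered discomfort at visits, 3 to 21 months | Yes |
| Other non-fatal events | None stated, unless volunteered as capsule discomfort | Yes |

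The weakness therefore lies in the last two rows.

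**How much under-recording costs**

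The plan has no figure of its own to reproduce here. The inputs are:
- 798 participants in total (Sample size, cognitive function study), so 798/2 = 399 per arm if split equally.
- True side-effect rates p0 and p1: assumed, because the article gives none.
- Share of events volunteered, s, taken as equal in both arms because the trial is double-blind with identical capsules: assumed.
- Two-sided 5% test: assumed.

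The recorded rates are a = s·p0 and b = s·p1. With m = (a + b)/2,

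power = Φ{ [ (b − a) − 1.96·SE0 ] / SE1 }, where SE0 = √[2m(1 − m)/n] and SE1 = √{[a(1 − a) + b(1 − b)]/n}.

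For 5% v 10%:
- Full capture (s = 1): m = 0.075, SE0 = 0.01865, SE1 = 0.01856. Power = Φ[(0.05 − 0.03655)/0.01856] = Φ(0.72) = 0.77.
- Half capture (s = 0.5), so 2.5% v 5%: m = 0.0375, SE0 = 0.01345, SE1 = 0.01342. Power = Φ[(0.025 − 0.02636)/0.01342] = Φ(−0.10) = 0.46.

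The ratio of the rates stays at 2, but the absolute difference halves while its standard error falls only from 0.0186 to 0.0134.

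The same formula over a range of assumptions gives:

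| True rates | All recorded | 75% | 50% | 25% |
|---|---|---|---|---|
| 5% v 10% | 0.77 | 0.63 | 0.46 | 0.26 |
| 10% v 15% | 0.57 | 0.44 | 0.31 | 0.17 |
| 10% v 20% | 0.98 | 0.92 | 0.77 | 0.46 |

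The 399 per arm ignores the 20% drop-out that the sample size section allows. With 399 × 0.8 ≈ 319 per arm, the first row becomes 0.67 with full capture and 0.38 at half capture. The level falls and the pattern is the same.

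**A check on the remedy**

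Recording every complaint brings in background events. If these were pooled with the capsule effects and added 20 percentage points to each arm (assumed), 5% v 10% would become 25% v 30%. Then SE0 = 0.03161 and SE1 = 0.03156, and power = Φ[(0.05 − 0.06196)/0.03156] = Φ(−0.38) = 0.35, below the 0.46 from half capture. Fuller recording therefore helps only if counts are kept separate by event type.

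**The case against.** A reader might infer that the committee cannot check safety at all, because all it receives is unprompted complaints. The article does not support that. Admissions for MI or stroke are taken from practice records throughout, death is an outcome, and consent is sought to use the NHS Central Register to follow health status. The committee is not confined to the discomfort record, and possible early stopping is tied to safety in general, not to side effects alone.

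A reader might also infer that a fall or a bleed would leave no record anywhere. That cannot be established. This is a journal article, and the full protocol, which is not shown, may hold procedures for serious or general adverse events.

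Three further arguments have weight. Blinding makes the loss roughly equal between arms, so a spurious difference is not the main risk. The nurses are trained and monitored centrally, so wide variation between them should not be presumed. The dose is described as achievable by diet and well below the level generally recognised as safe, so light tolerability recording could be a deliberate choice.

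All of this stands, and it limits the point. It does not remove it. The article does not leave side-effect capture to another document; it states a rule, and that rule is passive and depends on attribution. A separate procedure for serious events would not change how complaints are taken at visits. The committee is expected to interpret side-effect data, and the only source described for them is this rule.

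**Conclusion.** The point holds as a weakness in data collection. It is an improvement worth making and does not threaten the primary analysis. Comparison by arm of tolerability effects, and of non-fatal events other than MI or stroke admissions, is likely to rest on incomplete counts, mainly diluting true differences. Under the assumed 5% v 10% with 399 per arm, power falls from about 0.77 to 0.46 if half the events are volunteered. A difference as large as 10% v 20% would often still show.

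The size rests on assumed rates, an assumed share volunteered and equal under-reporting in the two arms. If participants guessed their allocation, under-reporting could differ by arm and the comparison could also be biased; nothing in the article shows that this would happen. The conclusion that capture is passive and lacks a 24-month item rests on the text alone.

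**What to change.** At each existing 3-monthly visit, and as an added item in the 24-month assessment, put the same two things to every participant:
1. One fixed open question, for example whether they have had any new or worse health problem since the last visit.
2. A tick-list of the four recognised effects the article already names.

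Record every answer whatever its presumed cause. Give the monitoring committee counts by arm separately for each event type, not pooled, so that background complaints do not mask a difference. If the full protocol already has adverse-event procedures, align the visit form with them.

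The cost is a form page and a few minutes at each of the eight visits (seven from 3 to 21 months, plus 24 months), with no extra staff or procedures. The downside is more minor complaints to code.
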